### Procedure for unblinding if needed {17b}

Not applicable.

## Data collection and management

### Plans for assessment and collection of outcomes {18a}

The properties of the MDAS, RASS, and NCI-CTCAE are described as follows:

#### The Memorial Delirium Assessment Scale

MDAS is a ten-item, four-point clinician-rated scale designed to quantify the severity of delirium in medically ill patients [13]. It has very good psychometric properties, with high reliability (*r* = .91) and good discriminant and concurrent validity. Though the scale was intended to assess patients based on all ten items, it was suggested that items in MDAS can be pro-rated in the event the patient is not able to communicate (Lawlor, et al., 2000). To conduct assessments as well as to ensure patient’s safety, the study team physician will make regular home visits to assess the patient at the time of the first dose, and then at 24 h, 48 h, and 72 h after the first dose.

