### Intervention description {11a}

Every 24 h, patients will receive two regular doses of either OT haloperidol 2.5 mg or OT olanzapine 5.0 mg with an interval of 12 h. Patients may also receive up to two breakthrough doses within a minimum interval of 1 h from the last dose when needed. In total, up to four doses of medication will be prepared. The dosage schedule is provided below in Table 2.

**Table 2 Tab2:** Dosage schedule for clinical trial

	Timing	Haloperidol	Olanzapine
First 24 h	First dose	2.5 mg	5.0 mg
	12 h later	2.5 mg	5.0 mg
	First breakthrough	2.5 mg	5.0 mg
	Second breakthrough	2.5 mg	5.0 mg
Second 24 h	First dose	2.5 mg	5.0 mg
	12 h later	2.5 mg	5.0 mg
	First breakthrough	2.5 mg	5.0 mg
	Second breakthrough	2.5 mg	5.0 mg
Third 24 h	First dose	2.5 mg	5.0 mg
	12 h later	2.5 mg	5.0 mg
	First breakthrough	2.5 mg	5.0 mg
	Second breakthrough	2.5 mg	5.0 mg
	Total dose prepared	30.0 mg (10.0 mg/day)	60.0 mg (20.0 mg/day)

The haloperidol preparation is a solution with concentration of 2 mg/mL of haloperidol. The medication is administered via dropper, where 20 drops is equal to 1 mL (1 drop = 0.05 mL). Standardized doses of 2.5 mg of haloperidol (25 drops or 1.25 mL) of the haloperidol preparation would be administered for each dose.

Olanzapine preparation is a 5 mg oro-dispersible tablet. Standardized doses of 5 mg will be delivered each time a dose is required.

After obtaining consent, the patient will be randomized into either the haloperidol or olanzapine group. Instructions on how to administer the medication will be provided to the caregivers; caregivers will also be advised to serve breakthrough doses of the assigned anti-psychotic drug as needed. Basic demographic information, including the patient’s age, sex, primary diagnosis, and co-morbidities, will be collected.

All relevant trial materials are prepared in packs with the following materials:
The required amount of medication (haloperidol or olanzapine),Rescue medication—subcutaneous midazolam with syringe and needle,A copy of the patient information sheet and informed consent form,Instructions for the caregivers on how to administer medication, andA copy of the case report form.

The investigators will provide the packs to the caregivers of enrolled patients. Additionally, the investigators will conduct daily clinical reviews at home over 72 h. They will confirm that the dosages used and the dosages documented are congruent.

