Subcutaneous injectable midazolam would be prepared as a rescue medication in the event delirium symptoms remain uncontrolled and distressing after the trial medication is depleted. Rescue medications will be used in any one of the following situations:
Within any of the 24-h periods, the patient remains uncontrollably agitated, despite all prepared doses of the treatment having been applied.Patient is unable to tolerate OT medication.Patient experiences severe toxicities from trial medication.

The caregiver will receive detailed instructions for the trial included with the case report forms. The forms will also provide support resources such as the hospice hotline and investigators’ contact number. Per clinical practice, the caregiver will give the first dose of medication under the supervision of the study team. Additionally, they will be instructed on how to rate the patient’s agitation and will provide the baseline rating with the investigator’s support. The study team physician will assess the patient’s baseline symptom severity.

Alongside drug therapy, usual non-pharmacological interventions will be provided to all patients. These interventions include (i) regularly orientating the patient; (ii) keeping the room bright during the day; (iii) minimizing the use of tubes, catheters, physical restraints, or other immobilizing devices; and (iv) minimizing unnecessary disturbances to the patient.

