## Assignment of interventions: allocation

### Sequence generation {16a}

The randomisation sequence is generated before the start of the study with 1:1 allocation using random block sizes of 2 and 4. With each successive recruitment, patients will be assigned to the treatment arm consecutively based on their sequence on the generated list. The patient will receive a Trial Identification Number based on their position of the sequence.

To begin the trial, Study personnel will collect assigned trial medication from the organization’s pharmacy and bring along to the home visit. The material packs prepared for the trial will then be marked in the order of the randomised allocation; this allows for the investigators to more easily and more quickly identify the pack to pick up and deliver to the patient.

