## Assignment of interventions: blinding

### Who will be blinded {17a}

This study was designed as an open-label study and thus there was no blinding between trial participants, care providers or the researchers.

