#### The Richmond Agitation-Sedation Scale modified for palliative care

The RASS is a simple observational instrument assessing levels of sedation and agitation. It requires no patient input and ranges from + 4 (overly combative) to − 5 (unarousable). It is considered less time-consuming and easier to use than other similar instruments [15]. Developed for adult intensive care unit patients, the scale demonstrated strong inter-rater reliability in that setting. A modified version was designed for use in the palliative care setting, which produced acceptable psychometric properties. Hui, et al. had caregivers using the RASS to assess patients, which gave ratings similar to clinicians [16]. As part of scoring calibration with the caregivers, the attending study team members will guide the caregivers to provide the first score during the time of the first dose. Subsequently, caregivers will chart the patient’s agitation using the RASS every 6 h after the first dose. If breakthrough medication is required, the caregiver will also chart the time of administration and provide a RASS score.

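### The visible text does not require baseline MDAS and RASS to be scored before the unblinded physician and caregiver know the arm, although the outcomes are reductions from that baseline

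*Protocol article*

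**What the plan says.** All references are to the protocol article.

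- **Randomisation.** Intervention description {11a}: "After obtaining consent, the patient will be randomized into either the haloperidol or olanzapine group".
- **Medication.** Sequence generation {16a}: "Study personnel will collect assigned trial medication from the organization’s pharmacy and bring along to the home visit". Implementation {16c} instead has investigators fetch the pack in connection with the consent visit and take it to the family. Intervention description {11a} makes haloperidol a solution given by dropper and olanzapine an oro-dispersible tablet. It also lists the case report form, information sheet and consent form among the pack contents.
- **Baseline MDAS.** The Memorial Delirium Assessment Scale: "the study team physician will make regular home visits to assess the patient at the time of the first dose", and then at 24, 48 and 72 h.
- **Baseline RASS.** The Richmond Agitation-Sedation Scale section: "the attending study team members will guide the caregivers to provide the first score during the time of the first dose". Intervention description {11a} says the caregiver "will provide the baseline rating with the investigator" in support, and that "the caregiver will give the first dose of medication under the supervision of the study team". It does not time the rating relative to that dose or to the allocation.
- **Blinding and concealment.** Who will be blinded {17a}: "there was no blinding between trial participants, care providers or the researchers". Concealment mechanism {16b} is marked not applicable.
- **Outcomes.** Outcomes {12} defines the primary outcome as the reduction in MDAS and the first secondary outcome as the reduction in RASS, with baseline as the first of four time-points.

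**The concern.** In an open-label trial with these two products the follow-up ratings are hard to protect from knowledge of the arm. The baseline rating can be protected, because it can be finished before anyone at the bedside learns the arm. The visible text does not secure this.

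Both scales leave room for judgement. The MDAS is clinician-rated and may be pro-rated when the patient cannot communicate. The first RASS comes from a caregiver who has only just been shown how to rate. A rater who expects more from one drug could, without intending it, score that drug's patients as worse at the start and so enlarge their apparent reduction.

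Objectives {7} describes a non-inferiority comparison of haloperidol against olanzapine. A shift in haloperidol's favour would make a false conclusion of non-inferiority more likely. A shift the other way would count against haloperidol.

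This is distinct from concealment at enrolment. Even if nobody could foresee the next arm when enrolling a patient, a baseline scored after the reveal would still be open to influence.

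**Working it through.** **1. Order of steps.** The plan states no figure on this point, so the check sets the sections side by side.

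| Step | Section | Position |
|---|---|---|
| Consent | {11a}, {16c} | First |
| Randomisation | {11a} | After consent |
| Assigned pack at the home | {16a} or {16c} | By the first dose, on either account |
| First dose, given by the caregiver | {11a} | Pack open, product visible |
| Baseline MDAS and RASS | {18a}, scale subsections | At the first dose |

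On either account of pack collection, randomisation and the assigned product come before or together with the baseline ratings. If the copy of the case report form in the pack is the one used for baseline, the pack must be opened to record it.

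**2. How a baseline shift enters the outcome.** Reduction = baseline − follow-up. Let the arm-related rating shift (haloperidol minus olanzapine) be b at baseline and f at follow-up. The between-arm difference in reduction then moves by b − f.

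- Shift at baseline only (f = 0): the difference moves by b, at 24, 48 and 72 h alike.
- Same shift throughout (f = b): the difference moves by 0.
- Opposite shifts (f = −b): the difference moves by 2b.

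**3. Scale against the plan's own yardstick.** Sample size {14} gives a minimal important difference of 2 MDAS points. With f = 0:

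- b = 0.5: 0.5/2 = 25%
- b = 1: 1/2 = 50%
- b = 2: 2/2 = 100%

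**4. Illustration of the effect on error.** Assumptions, none stated for this purpose in the article: the 2-point difference serves as the non-inferiority margin, the test is one-sided at 0.025, there are 32 patients per arm (Table 3), and the SD of the change is 7.64 (the Table 3 SD, there given for the score) or 5. The shift favours haloperidol, f = 0, and the true difference equals the margin.

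SE = SD × √(2/32) = SD × 0.25, which is 1.91 for SD 7.64 and 1.25 for SD 5.

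Error = 1 − Φ(1.96 − b/SE).

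| b (points) | SD 7.64 | SD 5 |
|---|---|---|
| 0 | 0.025 | 0.025 |
| 0.5 | 0.045 | 0.059 |
| 1 | 0.075 | 0.123 |
| 2 | 0.181 | 0.359 |

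For example, with b = 1 and SD 7.64: 1.96 − 1/1.91 = 1.436, and 1 − Φ(1.436) = 0.075. Every b here is assumed; the article gives no basis for its size.

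**The case against.** **The figures that would settle the order are missing.** Table 1 (the SPIRIT schedule) and Fig. 1 (the flowchart) are not shown, and either could put baseline before allocation. This stands and limits the certainty. If they do, the two scale subsections still need wording to match.

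**The first-dose phrase may only name the visit.** It sits alongside 24, 48 and 72 h and need not fix an order within the visit. Outcomes {12} also separates baseline from the times after commencement, which suggests a pre-drug value. This stands. A reader might infer that baseline is scored after the drug has been given; the text does not support that. What stays open is the order relative to knowledge of the arm.

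**A constant leaning would cancel.** The same kinds of unblinded rater score follow-up, so an equal shift at both times drops out, and protecting baseline alone would remove that cancellation. The algebra is right. But nothing in the plan makes the shifts equal, and shifts in opposite directions would add.

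**Reordering at the bedside is not enough.** Packs are marked in allocation order, blocks are of 2 and 4, concealment is marked not applicable, and the form travels with the drug. A physician could know or guess the arm whatever the order of scoring. This stands, and the fix has to cover the packs as well.

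**Open-label conduct was a deliberate choice.** The Discussion calls blinding procedures hazardous and without added value. That argument concerns masking treatment; scoring before the reveal masks no treatment.

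A reader might also infer that baseline is spoiled as an adjustment covariate. Statistical methods {20a} names a repeated-measures ANOVA and no baseline adjustment, so that harm is not tied to a planned analysis.

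**Conclusion.** The point holds as an avoidable gap. In the visible text, randomisation and the assigned, recognisable product come before or with the baseline ratings, and nothing shown requires MDAS and RASS to be recorded before the raters know the arm. That opens a route for bias into the primary and first secondary outcomes.

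The size of any bias is unknown. The one-for-one effect applies only to a shift that differs by arm and is not repeated at follow-up. One MDAS point, half of the 2-point minimal important difference, is an illustration and not an estimate. The documents do not show that bias will occur, or that the arm is known at baseline in every patient.

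The conclusion rests on the text alone and would soften if Table 1 or Fig. 1 puts baseline before the reveal. The change is cheap enough to be worth making, and the gap is not a reason to doubt the trial as a whole.

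**What to change.** 1. **The two scale subsections.** Replace the timing in the MDAS sentence ("the study team physician will make regular home visits to assess the patient at the time of the first dose") and in the RASS sentence ("guide the caregivers to provide the first score during the time of the first dose"). Suggested wording: *Baseline MDAS, and baseline RASS with guidance, are scored and entered on the case report form with clock time after consent and before the allocation is revealed; the first dose follows.*
2. **Intervention description {11a}.** Add the same order where the baseline ratings are described, since no timing is given there now.
3. **Pack contents, {11a}.** Keep the case report form, information sheet and consent form outside the medication pack, so that baseline can be recorded with the pack closed.
4. **Sequence generation {16a} and Concealment mechanism {16b}.** Use closed, externally identical, sequentially numbered packs, and state that the visiting physician does not learn the arm until baseline is locked. Replace the not-applicable entry accordingly.
5. **Table 1 and Fig. 1.** Check that both show this order.

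**Cost.** Slightly more pack preparation, and the first dose comes after the baseline scoring instead of alongside it. No added visit or staff.

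**Limits.** Follow-up ratings stay open-label. With blocks of 2 and 4 in an unblinded trial, the next arm may sometimes still be guessed.

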#### The Richmond Agitation-Sedation Scale modified for palliative care

The RASS is a simple observational instrument assessing levels of sedation and agitation. It requires no patient input and ranges from + 4 (overly combative) to − 5 (unarousable). It is considered less time-consuming and easier to use than other similar instruments [15]. Developed for adult intensive care unit patients, the scale demonstrated strong inter-rater reliability in that setting. A modified version was designed for use in the palliative care setting, which produced acceptable psychometric properties. Hui, et al. had caregivers using the RASS to assess patients, which gave ratings similar to clinicians [16]. As part of scoring calibration with the caregivers, the attending study team members will guide the caregivers to provide the first score during the time of the first dose. Subsequently, caregivers will chart the patient’s agitation using the RASS every 6 h after the first dose. If breakthrough medication is required, the caregiver will also chart the time of administration and provide a RASS score.

#### National Cancer Institute Common Terminology Criteria for Adverse Events [17]

Possible side effects of taking either drug include over sedation and extrapyramidal symptoms (akathisia, extrapyramidal disorder, and spasticity). To track these adverse events and their severity, the study team physician will rate observed adverse events using the scale provided by the criteria at 24 h, 48 h and 72 h.

The trial will be conducted for up to 72 h after recruitment; the trial may be stopped earlier in the event of the patient’s death or to ensure the patient’s safety and well-being. If the patient completes the trial and survives, the patient will continue to receive support from their palliative care providers. Patients who survive beyond 7 days after recruitment will be excluded from per-protocol analysis, as they no longer fit the inclusion criteria for the study, i.e. no longer imminently dying.

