**Methods:**

Eighty patients with a prognosis of 7 days or less will be recruited for an open-label randomised control trial. The two arms compare oral-transmucosal haloperidol 2.5 mg vs olanzapine 5 mg over 72 h. The severity of agitation, delirium and toxicities of treatments will be compared at the 24th, 48th and 72nd hour after drug administration.

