## Introduction

### Background and rationale {6a}

Terminal delirium is a common syndrome in palliative care. It occurs within the final days of life in between 25 and 88% of dying patients and is perceived to be one of the most difficult end-of-life symptoms to manage [1]. In contrast to other types of delirium that are treatable (and hence reversible), terminal delirium is a complex and refractory syndrome that is often multi-factorial in aetiology. It is characterised by a diminished level of consciousness, an inability to focus or maintain attention, and a disturbance of cognition and perception (e.g. hallucination, agitation, and restlessness).

Delirium could have a profound impact on the well-being of the patients as well as the family caregivers. Family caregivers perceived a high level of stress both physically and psychologically in the management of delirious patients [2]. Similar distress was also observed by the investigators in the home-based hospice setting. Within community care, pharmacological therapies are utilised to manage the syndrome, the most commonly used being neuroleptics haloperidol and olanzapine.

Haloperidol is the first of the butyrophenone series of major antipsychotics. The mechanism of action of haloperidol for the treatment of psychotic disorders is unclear. However, its efficacy could be mediated through its activity as an antagonist of central dopamine type 2 receptors. Haloperidol also binds to alpha-1

adrenergic receptors, but with lower affinity, and displays minimal binding to muscarinic, cholinergic, and histaminergic (H_1_) receptors.

Olanzapine is a second-generation thienobenzodiazepine antipsychotic which displays potent antagonism of serotonin 5-HT2A and 5-HT2C, dopamine D1-4, histamine H1, and alpha1-adrenergic receptors. Olanzapine shows moderate antagonism of 5-HT3 and muscarinic M1-5 receptors, and weak binding to GABA-A, BZD, and beta-adrenergic receptors. Although the precise mechanism of action in schizophrenia and bipolar disorder is not known, the efficacy of olanzapine is thought to be mediated through combined antagonism of dopamine and serotonin type 2 receptor sites.

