### Outcomes {12}

The primary outcome is the reduction in delirium severity as measured with the Memorial Delirium Assessment Scale (MDAS). Secondary outcomes are the reduction in the severity of agitation as measured with the Richmond Agitation-Sedation Scale modified for palliative care (RASS), and the frequency and severity of medication toxicities, as measured using the National Cancer Institute Common Terminology Criteria for Adverse Events (NCI-CTCAE). These data will be collected over four time-points: (i) baseline, (ii) 24 h after commencement, (iii) 48 h after commencement, and (iv) 72 h after commencement.

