## Statistical methods

### Statistical methods for primary and secondary outcomes {20a}

For the first primary outcome, changes to the severity of delirium over three 24-h periods, as measured with the MDAS, would be analysed using repeated-measures, between-factors ANOVA. If a statistically significant difference is found between medications, post hoc analysis will be conducted to analyse the change in MDAS scores at each time-point.

The second outcome, changes in the patient’s agitation, will be measured using the RASS score. Similarly, the repeated-measures, between-factors ANOVA would be used to analyse the differences in scores.

Additional outcomes of interest are possible toxicity effects due to the medication, which is measured using NCI CTCAE. For each group, the frequency of toxicities (Akathisia, Extrapyramidal disorder, and spasticity) for each group will be compared.

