### Adverse event reporting and harms {22}

Related adverse events are defined as events where there is a reasonable possibility that the adverse event (AE) may have been caused by participation in the clinical trial. Relatedness may be graded as one of three options: definitely, probably, or possibly.

Any complaints, adverse event, serious adverse event, or incidence must be reported to the Principal Investigator. Follow-up information will be actively sought and submitted as it becomes available. All related AEs will be recorded and filed as a Research Incident Report Form in the patient’s study file.

For all AEs, the study team and the medical director of HCA will be notified to review the incident and discuss changes or improvements to be made to address the complaint. For serious AEs, a report will be submitted to both the IRB and the Health Sciences Authority (HSA).

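### The protocol contradicts itself on whether CTCAE toxicity is rated before the first dose, and its toxicity comparison makes no use of a baseline

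*Protocol article*

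**What the plan says.** Four places in the protocol article bear on the timing and use of the toxicity ratings.

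- **Outcomes {12}** names MDAS, RASS and NCI-CTCAE and then says of all three: "These data will be collected over four time-points: (i) baseline, (ii) 24 h after commencement", followed by 48 h and 72 h.
- **The section on the NCI-CTCAE instrument**, which tells the physician what to do, says "the study team physician will rate observed adverse events using the scale provided by the criteria at 24 h, 48 h and 72 h". It names no baseline rating. It introduces the signs to be tracked with "Possible side effects of taking either drug include over sedation and extrapyramidal symptoms (akathisia, extrapyramidal disorder, and spasticity").
- **The abstract (Methods)** says that "toxicities of treatments will be compared at the 24th, 48th and 72nd hour after drug administration".
- **Statistical methods {20a}** says that "the frequency of toxicities (Akathisia, Extrapyramidal disorder, and spasticity) for each group will be compared". It mentions no change from baseline, no restriction to new or worsened events, and no use of relatedness.

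The Background section says of terminal delirium: "It is characterised by a diminished level of consciousness". It adds, among other features, "a disturbance of cognition and perception (e.g. hallucination, agitation, and restlessness").

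**The concern.** Recording the frequency and severity of toxicity from treatment is the trial's stated secondary objective. Every patient enters with diagnosed delirium, which the protocol itself describes as including agitation and restlessness. Akathisia is one of the three terms to be compared, and at the bedside it can look much like that restlessness. Without a rating of the same term before the first dose, the physician at 24 h has no like-for-like reference for what was already there.

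If pre-existing signs enter the counts, the absolute toxicity rates of both drugs are too high and the contrast between them is too small. A real difference in toxicity is then easier to miss, and the result leans towards a conclusion that the drugs are similar. A baseline rating cannot be reconstructed once dosing has begun, so the conflict has to be settled before enrolment.

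**Working it through.** The protocol states no figure for toxicity, so there is none to reproduce. The check is a comparison of the text, followed by an illustration.

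**Step 1: rating times, section by section.**

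| Section | First-dose or baseline rating | Later ratings |
|---|---|---|
| Outcomes {12} (all three instruments) | yes | 24, 48, 72 h |
| MDAS section | yes, at the first dose | 24, 48, 72 h |
| RASS section | yes, at the first dose | every 6 h |
| CTCAE section | not named | 24, 48, 72 h |
| Abstract, toxicity comparison | not named | 24, 48, 72 h |

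The MDAS and RASS sections each state the first-dose rating explicitly. Only the CTCAE section leaves it out, so the omission is hard to read as shorthand.

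**Step 2: does the analysis repair it?** The statistical methods compare frequencies by group and use no baseline. Even if the Outcomes section governs and a baseline rating is taken, the article gives that rating no role.

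**Step 3: what other baseline information exists?**

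- The physician assesses symptom severity at baseline, but no CTCAE term is named.
- The first-dose RASS score covers sedation and general agitation. It does not rate akathisia, extrapyramidal disorder or spasticity, the three terms compared.
- The adverse-event section says "Relatedness may be graded as one of three options: definitely, probably, or possibly". That grading is not tied to the toxicity comparison, and no unrelated grade is listed.

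**Step 4: illustration of size.** Let p0 be the share of patients with the sign before dosing, equal in both arms in expectation, and e the treatment-emergent rate among the others. If every pre-existing sign is counted,

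observed rate = p0 + (1 − p0) × e,

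so the risk difference shrinks by the factor (1 − p0). Assume e = 10% in one arm and 20% in the other. Neither these rates nor any value of p0 comes from the documents.

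| p0 | Arm with e = 10% | Arm with e = 20% | Difference | Ratio |
|---|---|---|---|---|
| 0% | 10% | 20% | 10 points | 2.00 |
| 10% | 0.10 + 0.90 × 0.10 = 19% | 0.10 + 0.90 × 0.20 = 28% | 9 points | 1.47 |
| 30% | 0.30 + 0.70 × 0.10 = 37% | 0.30 + 0.70 × 0.20 = 44% | 7 points | 1.19 |
| 50% | 0.50 + 0.50 × 0.10 = 55% | 0.50 + 0.50 × 0.20 = 60% | 5 points | 1.09 |

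At p0 = 30%, 0.30/0.37 = 81% and 0.30/0.44 = 68% of the counted cases would have been present before treatment.

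**Step 5: effect on power.** Take 40 patients per arm (the target of 80, split equally), two-sided alpha 0.05 and a normal approximation. For 10% against 20%, power is about 24% with no pre-existing signs and about 9% at p0 = 30%. For an assumed larger contrast of 10% against 25%, power is about 42% at p0 = 0, then 28%, 16% and 10% at p0 = 10%, 30% and 50%.

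**The case against.** The strongest reply is that a baseline rating is already planned. The Outcomes section says so, and the two sections can be read together: data collected at baseline, and post-dose events rated at the three later visits. The schedule in Table 1 might settle the question, but it is a figure that is not shown. This stands in part. It cannot be said that no baseline rating will be taken. But the instruction to the physician still omits it, and would need correcting whatever the table shows.

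Second, attribution is partly handled. The physician sees the patient at the first dose, and relatedness is to be graded. This also stands in part, and it is why separation is unreliable rather than impossible. The relatedness grading is not linked to the comparison, and it would be made with allocation known, because the trial is open-label.

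Third, a definition of treatment-emergent events is commonly left to the statistical analysis plan, and its absence alone would be no finding. That is fair. It matters here because the protocol conflicts on whether the rating such a definition needs will exist.

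Fourth, the trial has little power for toxicity in any case, and the objective is to record toxicity. For 10% against 20%, power is low even without dilution. The inflated absolute rates would still affect a purely descriptive report.

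A reader might also infer several stronger points that the documents do not support:

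- **Pre-existing signs are counted as drug toxicity.** The protocol does not say this. It would follow only if the CTCAE section governs and clinical judgement removes nothing.
- **Drowsiness contaminates the comparison.** Over-sedation is tracked but is not among the three terms compared, and sedation has a first-dose RASS score.
- **Spasticity is already present from dying or delirium.** The protocol does not describe it as a feature of either.
- **Patients could be stopped for signs they had at entry.** The discontinuation criterion concerns intolerable toxicity related to the trial medication, so it already calls for a judgement of relatedness.

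**Conclusion.** The point holds as an internal contradiction with a moderate consequence for a secondary outcome. The Outcomes section and the CTCAE section disagree on whether toxicity is rated at baseline, and the stated comparison uses no baseline. If the CTCAE section is followed, pre-dose signs, most plausibly restlessness resembling akathisia, cannot be reliably told apart from treatment-emergent ones.

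Because randomisation balances such signs on average, the expected result is higher absolute rates and a smaller difference, not an advantage to either drug. The calculated sizes are illustrations only. They rest on assumed emergent rates, assumed pre-existing shares, and the worst case in which every pre-existing sign is recorded as toxicity. To the extent that the physician discounts some of these signs, the dilution is smaller.

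**What to change.** 1. Align the CTCAE section with the Outcomes section: the study physician rates the same CTCAE terms before the first dose, and again at 24, 48 and 72 h. Check that the schedule in Table 1 agrees.
2. In the statistical methods, state that a term counts as toxicity when it is new or of higher grade than at baseline, and that these events are compared between arms.

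The physician already attends at the first dose for the MDAS. The cost is a few minutes at that visit, one more column on the case report form and a sentence in the analysis section. No extra visit or staff is needed. The change has to be made before enrolment, because the rating cannot be recovered after dosing.
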